| **2.1**  **Research question/objective(s) of the study** | The aim is to assess the association between antibiotic use and risk of subsequent urinary tract infections in adults.  ***Background***  Urinary tract infections (UTIs) encompass a spectrum of infectious syndromes that affect the urinary tract anywhere from the urethra to the kidneys and are one of the most common infections, particularly in primary care (Al Hawati, Blair & Larnard). In 2023, the UTI incidence in primary care was 20 cases per 1.000 registered men and 117 cases per 1.000 registered women (Nivel, 2024). Not only is the UTI incidence higher in women than men, it also increases with age (Ahmet et al., 2018).  Women are particularly susceptible due to the close proximity of the rectum to the urethra as well as a relatively short urethral length (Li & Leslie, 2023). It is reported that 50-60% of women have at least one UTI in their lifetime (Al Hawati, Blair & Larnard, 2023). Most UTI are caused by bacteria from the gut  (Worby et al. 2022).  Most patients with UTIs can be treated relatively simple with oral antibiotics, although treatment failure occurs. Around 20-30% of women with an initial UTI will experience a recurrent UTI within 3-4 months of initial infection (Foxman, 2003). Furthermore, some UTIs can become complicated through a pyelonephritis, prostatitis, and urosepsis, which are associated with morbidity and mortality (Sabih & Leslie, 2023).  A healthy vaginal microbiota is low-diverse and dominated by *Lactobacillus crispatus*.  Vaginal lactobacilli have been touted to prevent invasion of uropathogens, for instance by creating an acidic environment. Disruption of the vaginal ecosystem, causing an overgrowth of anaerobic bacteria or yeasts, increases the risk of vaginal infections such as sexually transmitted infections (Stapleton, 2016, Herthelius 1988). Conversely, treatment that restores a Lactobacillus-dominated microbiota is associated with lower risk of recurrent UTIs. Usage of antibiotics can alter the microbial community (Chee, Chew & Than, 2020).  In pre-menopausal women, factors related to sexual behaviour are major risk factors for UTIs. These include: having a new sexual partner, increased frequency of sexual intercourse as well as the use of spermicide-containing contraceptives (Hooton, 2001). Sexual behaviour is less firmly associated with UTIs in post-menopausal women, where age-, hormonal- and disease-related urogynaecology and immune factors play a more prominent role. An increased postvoid residual urine volume, the presence of bladder prolapse and urinary incontinence have been associated with UTIs (Athanasiou et al., 2010). Antibiotic use or treatment of asymptomatic bacteriuria has also been associated with the development of UTIs (Cai et al., 2014, Smith et al. 1997).  To date, only one small-scale study has been conducted on this subject, which indicated a potential correlation between antibiotic use and an elevated risk of urinary tract infections in pre-menopausal women (Smith et al. 1997). To our knowledge, there are no studies whether this also holds for postmenopausal women and men.  In this study, we would like to evaluate whether different antibiotics (either to treat UTI or other infections) are associated with increased risk of UTI in premenopausal women, postmenopausal women and men. If this association can be confirmed, the next would be to study effective preventive measure for an UTI. This would be highly beneficial, as urinary tract infections represent a significant burden for patients, while antibiotic use is also the major contributing factor to the development of antibiotic resistance. |

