| --- | --- |

1. **Study design**

| **3.1**  **a. General description of the study design** | This research project will use the data infrastructure Extramural Leiden Academic Network (ELAN).  ELAN provides access to and the use of pseudonymized healthcare data from various cooperating partners such as healthcare data of general practitioners. The study period concedes 2014-2024.  ***Question***  Is antibiotic use associated with increased risk for urinary tract infection in adults?  Further explorations will be done to what extent the increased UTI risk of antibiotic use holds for:   - Different antibiotics or antibiotic classes - Men versus women - Post- versus Premenopausal women - Indication for antibiotic treatment (excluding UTI’s)   A self-controlled cases series (SCCS) design will be employed to establish the risk for developing an UTI within 3 months after antibiotic treatment compared to patients with an UTI who did not receive an antibiotic treatment. With the SCCS design, patients will be their own control.  The primary endpoint is risk of a UTI within 3 months after initiation of antibiotic treatment computed as an odds ratio.  An antibiotic treatment is defined as the exposure. An UTI between 2 weeks and 3 months after antibiotic treatment is defined as an event. The first 2 weeks after start of the treatment, patients are still somewhat protected by the antibiotic use against a new infection. And if a new antibiotic treatment is needed within 2 weeks after start of treatment, this is considered as treatment failure of the initial treatment.  Descriptive analysis will be performed for exposures, outcomes and covariables for the whole population of analysis and stratified by antibiotic use or not.  Multivariable logistic regression analysis will be performed to assess whether there is an association of antibiotic use with developing a UTI within 3 months after initiation of treatment. First a crude model will be used followed by confounder adjusted models. Confounders are season variability (Winter, spring, summer and autumn) and risk factors for UTI and selected based on theory or literature (Tj VanderWeele 2019). Risk factors are a history of an UTI, urine incontinence, urolithiasis, pregnancy, urine catheter, anatomical / functional abnormality urinary tract, immunocompromising comorbidities such as HIV/AIDS ,Type 2 Diabetes Mellitus.  **Subgroup analysis**  Subsequently, subgroup analysis will be performed to examine whether the association differs upon specific type of antibiotic treatment. For each subgroup, we will calculate an odds ratio for an UTI after antibiotic treatment. Subgroups are antibiotic(group)s, gender and age, type of infection and social determinants .  *Most used antibiotic(group)s in primary care*:   - Amoxicillin - Amoxicillin/clavulanic acid - Flucloxacillin - Tetracyclines - Macrolides - Fluoroquinolones - Trimethoprim - Co-trimoxazole - Fosfomycin - Nitrofurantoin   *Type of infection*   - All infections - UTI - non-UTI (all other infections)   *Gender and age*   - Men - Premenopausal women, defined as < 50 years of age - Postmenopausal women, defined as ≥ 50 years of age   *Social determinants*   - Socio-economic status (SES) - Migrant background |

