| --- | --- |
| **3.2**  **a. When will the study be conducted?**  **b. What is the intended end date of the study?** | The research will be performed as part of a MSc. Internship ([name]) in the period between February 2025 and June 2025.  Month 1 – Literature research, writing the introduction, first part of data preparation.  Month 2 – Writing the introduction and methodology, second part of data preparation.  Month 3 – Completing the introduction, methodology and data preparation, start of data analysis.  Month 4 – Completing the data analysis and writing the results.  Month 5 – Writing the report, focusing on the discussion.  The end date is July 2025. |
| **3.3**  **Does the study involve exclusively existing (patient) data (retrospective) and not data yet to be generated (prospective)?** | This study includes already existing data only, and is thus retrospective (see also 3.1). |
| **3.4**  **What type of data will be used for the research?** | Pseudonymized routine care patient data from GP practices participating in ELAN. |
| **3.5**  **If information from patient records is used: describe what type of information is involved.** | The dataset from ELAN contains data over a period of 10 years and includes:   - Number of all included patients in ELAN per year - All patients with an UTI   - ICPC code U70, U71, including subcodes   - Date of registration with GP office - Antibiotic prescriptions ATC J01 for all patients with an UTI   - Corresponding medical diagnosis with the antibiotic prescription by ICPC code   - Details on the antibiotic prescription (name of antibiotic, dose and duration) - Characteristics of included patients   - Year of birth   - Year of death   - Sex   - Referral to urologist for recurrent UTIs   - Risk factors for an UTI     - History of UTI ICPC code U70, U71     - Urine incontinence ICPC code U04     - Urolithiasis ICPC code U95     - Urine catheter ICPC code U28     - Anatomical / functional abnormality urinary tract ICPC code U85     - Type 2 Diabetes Mellitus ICPC code T90.02     - Prostate hypertrophy ICPC codes Y06, Y85     - Medication use for miction problems with ATC codes     - G04BD     - G04C     - Social economic status     - Migrant background |
| **3.6**  **To which time period do the data relate?** | The period between 2014 and 2024 |

1. **Data storage and privacy**

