| **4.10**  **If coding takes place: when will coding occur, by whom, and in what manner?** | Coding is done by STIZON and CBS |
| **4.11**  **Has a notification of the intended data processing been submitted via:**  <https://www.albinusnet.nl/weten-en-regelen/juridische-zaken/privacy/meldenverzamelenonderzoeksdata/>**?** | Yes |
| **4.12**  **If applicable: where will the coded data be stored, and who will have access to the coded data?**  **If applicable: where will the uncoded data be stored, and who will have access to the uncoded data?** | The coded data is stored, and a specific research folder assigned to the department disk (I: \) of PHEG. Only the researchers involved ([name] and [name]) and the PHEG data manager have access to this folder.  There is no storage of uncoded data. |
| **4.13**  **What technical and organizational measures have been taken to prevent loss, theft, or unauthorized use of the research data? For example, is a data safe being used?** | The data never physically leaves the research folder of the LUMC or the remote access CBS environment and see 4.12. |
| **4.14**  **By whom is the code key managed?** | STIZON. |
| **4.15**  **Will (research) data be shared with another institution(s) within the Netherlands and/or the EU?** | No. |
| **4.16**  **a. Will (research) data be shared with another institution/organization outside the EU?**  **b. Will the relevant patients be asked for consent to share their personal data with a country outside the EU?** | No.  Not applicable. |
| **4.17**  **How long will the (research) data be retained? If the data will be kept for longer or shorter than the standard retention period of 15 years, please explain why.** | After processing, the research data is returned to ELAN in accordance with the data transfer agreement. The LUMC department PHEG will keep the research data for 15 years. |

1. **Research population**

| **5.1**  **Inclusion criteria** | Adults patients 18 year and older with an acute UTI and registered at an GP office for a least 1 year |
| --- | --- |
| **5.2**  **Exclusion criteria** | Patients younger than 18 years of age.  Patients with antibiotic prophylaxes  UTIs are excluded as an event if   - During pregnancy - within 3 months after giving birth - within 1 year prior to an UTI (wash-our period) |

1. **Statistical analysis**

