| **6.1**  **a. Primary outcome**  **b. Secondary outcome** | ***Primary outcome***  What is the association of antibiotic use for any infection with risk for urinary tract infection in adults?   - Odds ratio for an UTI after antibiotic use in the preceding 3 months   - Per infection group, antibiotic for     - All infections     - An UTI     - An infection expect UTI’s   - Per antibiotic (group)   - Per patient group     - Men     - Women < 50 years of age     - Women ≥ 50 years of age   - Social determinants     - SES     - Migrant background   - Combinations of each subgroup   ***Secondary outcome***   - Hazard ratio for an UTI after antibiotic use in the preceding 3 months   - Per infection group, antibiotic for     - All infections     - UTI     - non-UTI   - Per antibiotic group   - Per patient group     - Men     - Women < 50 years of age     - Women ≥ 50 years of age   - Social determinants     - SES     - Migrant background   - Combination of each subgroup - Incidence of an UTI per month |
| --- | --- |
| **6.2**  **a. Statistical analysis primary outcome**    **b. Statistical analysis secondary outcome** | ***Primary outcome***  The Odds ratio for an UTI after antibiotic treatment the preceding 3 months will be calculated through a logistic regression model.  Risk factors and season variability are defined as confounders in this logistic regression model. Risk factors are a history of an UTI, urine incontinence, urolithiasis, pregnancy, urine catheter, anatomical / functional abnormality urinary tract and Type 2 Diabetes Mellitus. An Odds ratio for an UTI will be attributed to each confounder based on a critical literature appraisal.  ***Secondary outcome***  Cox proportional hazard regression models will be used to examine the associations between an UTI after antibiotic treatment the preceding 3 months.  Survival time (in days) was defined as the period between 14 days after the start of the antibiotic treatment and an UTI. The hazard ratio will be adjusted with the previous described confounders (see primary outcome).  The incidence of each UTI will be calculated for each month during 10 years to examine the season variability. |

1. **Appendices and references**

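### The confounder lists leave out age and sex, which the protocol names as UTI determinants and extracts, and include pregnancy, although UTIs in pregnancy cannot be events

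*Protocol*

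**What the plan says.** On adjustment, section 6.2 states: "Risk factors and season variability are defined as confounders in this logistic regression model". It then lists them: "Risk factors are a history of an UTI, urine incontinence, urolithiasis, pregnancy, urine catheter", followed by urinary tract abnormality and type 2 diabetes. It adds that each confounder will be given an odds ratio taken from a literature appraisal. Section 3.1 has the same list plus "immunocompromising comorbidities such as HIV/AIDS". Neither list contains age or sex. The secondary Cox model takes over the 6.2 list.

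On age and sex, the background in 2.1 says: "Not only is the UTI incidence higher in women than men, it also increases with age". It gives the yearly incidence as "20 cases per 1.000 registered men and 117 cases per 1.000 registered women". Year of birth and sex are both in the 3.5 extract. In the analysis they appear only as subgroups: men, and women split at 50 ("Premenopausal women, defined as < 50 years of age" and its counterpart).

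On pregnancy, section 5.2 does not count a UTI as an event if it occurs "During pregnancy" or within 3 months after birth. It excludes events and does not mention the corresponding time at risk. The 3.5 extract names no pregnancy or delivery item.

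**The concern.** A variable that influences both antibiotic prescribing and UTI confounds any between-person comparison that does not adjust for it. The protocol identifies age and sex as strong determinants of the outcome and holds the data, but fixes an adjustment set without them. This is not a detail left to a later analysis plan, because the list is spelled out twice.

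The overall odds ratio is at stake, as are the estimates by antibiotic and by indication that pool men and women of all ages. If prescribing differs by sex or age, part of the reported association would reflect who receives antibiotics.

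Pregnancy is the reverse problem: a covariate is kept for a state in which the plan allows no event to be counted.

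**Working it through.** **1. Does the design remove the problem?** Section 3.1 declares a self-controlled case series with patients as their own controls, but also describes a comparison with UTI patients who received no antibiotic. Section 6.2 specifies logistic and Cox regression and does not mention conditioning on the person. In those models sex does not cancel. In a conditional case series it would, but age changes over 2014-2024 and would still need a term. So age is missing on either reading, and sex is missing from the models as written.

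**2. Size of the sex bias.** The plan gives no figure to reproduce. From 2.1, the yearly rates are 117 and 20 per 1,000, a ratio of 117/20 = 5.85. Dividing by 4 gives quarterly risks of 0.02925 in women and 0.00500 in men. Assumed, because the documents do not give them: equal numbers of men and women registered; quarterly antibiotic use of 5% or 10% in men and f times that in women; no antibiotic effect within either sex; independent quarters.

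With w the share of women, p_w and p_m the antibiotic use, and r_w and r_m the quarterly risks:

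- risk if exposed: E = [w·p_w·r_w + (1−w)·p_m·r_m] / [w·p_w + (1−w)·p_m]
- risk if unexposed: U = the same with 1−p_w and 1−p_m in place of p_w and p_m
- crude OR = [E/(1−E)] / [U/(1−U)]

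All registered adults (w = 0.5), f = 2, p_m = 0.05: E = 0.02117, U = 0.01680, OR = 1.27.

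Among UTI patients, meaning at least one UTI in 40 quarters, the probability of inclusion is 1 − (1 − 0.02925)^40 = 0.695 for women and 1 − (1 − 0.005)^40 = 0.182 for men. Women make up 0.695/(0.695 + 0.182) = 79%. The quarterly risks become 0.02925/0.695 = 0.0421 and 0.005/0.1817 = 0.0275, a ratio of 1.53. For f = 2, p_m = 0.05: E = 0.0404, U = 0.0389, OR = 1.04.

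| f (women:men) | UTI patients | All registered adults |
|---|---|---|
| 1.0 | 1.00 | 1.00 |
| 1.2 | 1.01 | 1.07 |
| 1.5 | 1.02-1.03 | 1.16-1.17 |
| 2.0 | 1.04 | 1.27-1.30 |

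Ranges cover 5% and 10% use in men; the true OR is 1.00 throughout.

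A simulation of 60,000 adults over 40 quarters (true OR 1.5, use 10% in women and 5% in men) agrees. All adults: 1.88 pooled, 1.49 stratified by sex. UTI patients only: 1.55 pooled, 1.49 stratified. Conditional case series: 1.47.

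The document gives no age-specific rates, so no figure is offered for age.

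**3. Pregnancy.** A woman pregnant when the antibiotic starts who has a UTI within the 3-month window has it either in pregnancy or, if she has given birth, within 3 months of birth. Section 5.2 excludes both. An indicator of current pregnancy therefore has no events.

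Illustration with assumed inputs: 200,000 records, 3% pregnant, antibiotic use 15% if pregnant and 8% otherwise, baseline risk 2.9%, true OR 1.5, no events in pregnancy.

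- *Term fitted:* the coefficient is −3.1, −8.1, −18.1 and −28.1 after 5, 10, 20 and 30 iterations, with the standard error rising from 0.2 to about 55,000. There is no finite estimate. The antibiotic OR is 1.52, the same as when pregnant records are dropped.
- *Literature OR of 2 or 3 imposed:* the antibiotic OR moves to 1.44 or 1.41, because a raised risk is assigned to records that cannot have an event.

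**4. Do the lists agree?** Immunocompromising conditions are in 3.1 but not in 6.2; of these, only diabetes is in the 3.5 extract. "Prostate hypertrophy ICPC codes Y06, Y85" and micturition drugs (G04BD, G04C) are extracted as risk factors but are in neither adjustment list.

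**The case against.** The strongest reply is that the declared design is self-controlled, so sex and every other fixed trait cancels. That holds for a conditional analysis and would leave only age to handle. It does not hold for the models that 6.2 specifies.

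A reader might infer from the 5.85-fold incidence ratio that the main odds ratio could be inflated by up to about 30%. The documents do not support that for the planned population. Section 5.1 includes adults with a UTI, and 3.5 extracts prescriptions only for patients with a UTI. Section 4.5 speaks of all adults, but an all-adult model could not be fitted without prescriptions for the rest. Among UTI patients the sex contrast shrinks to about 1.5-fold and the bias to a few per cent. Adjusting for UTI history may absorb some of that.

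Nor is every antibiotic or indication estimate unadjusted. Section 6.1 plans results for men, women under 50 and women of 50 and over, and combinations of subgroups. These remove sex and split women coarsely by age. Men are not split by age, and the pooled estimates remain unadjusted.

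A reader might also infer that the pregnancy term undermines the primary result. If it is fitted, it does not: the antibiotic odds ratio is unchanged. The distortion arises only if a literature value is imposed, which is what 6.2 appears to describe. The argument also assumes that the covariate means current pregnancy. A covariate for any past pregnancy would have events, but the plan does not describe one.

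Finally, the immunocompromise wording in 3.1 can be read as giving diabetes as an example, so only the other conditions are unaccounted for. Extracting prostate and micturition variables does not oblige the plan to adjust for them.

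**Conclusion.** The point holds in a limited form. Age and sex should be in the adjustment set, and the protocol's own background and data extract support this. Sex is needed wherever the model is not conditional on the person; age is needed in every model.

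The expected sex bias is modest in the included population: about 1.01 to 1.04 for a true odds ratio of 1.00. It would be about 1.07 to 1.30 only if all registered adults were analysed. Both ranges rest on assumed antibiotic use 1.2 to 2 times as high in women, and the bias is nil if use is equal. The age bias cannot be sized from the document.

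The pregnancy conflict is a plain inconsistency between 3.1, 3.5, 5.2 and 6.2. Its effect on the antibiotic odds ratio is none if the term is fitted and, in the illustration, a shift from 1.52 to 1.44 or 1.41 if a literature value is imposed. With no pregnancy or delivery item listed in 3.5, the stated exclusion has no listed data to rest on.

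**What to change.** - In 3.1 and 6.2, add age (a spline or 5-year bands, time-varying) to every model, and sex to every model that is not conditional on the person. State which models are conditional.
- Drop pregnancy as a covariate. Remove pregnant time and the 3 months after birth together with their events, in exposed and reference time alike.
- Add pregnancy and delivery codes to the 3.5 data request.
- Use one confounder list in 3.1, 3.5 and 6.2, and state whether immunocompromising conditions other than diabetes are extracted or dropped. Adjusting for prostate hypertrophy and G04BD/G04C use is optional.

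The cost is small: revised wording, two covariates already extracted, a few extra codes, and the loss of some person-time that could contribute no events.

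### Section 6.2 takes the confounders' odds ratios from the literature, while section 3.1 uses the literature only to select confounders; the two must be reconciled, with the coefficients estimated in ELAN

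*Protocol*

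**What the plan says.** Section 6.2 fixes the primary analysis in three steps. The model is logistic: "The Odds ratio for an UTI after antibiotic treatment the preceding 3 months will be calculated through a logistic regression model". The covariates are named: "Risk factors and season variability are defined as confounders in this logistic regression model". The risk factors are UTI history, urinary incontinence, urolithiasis, pregnancy, catheter, urinary tract abnormality and type 2 diabetes, seven in all. Then comes the sentence at issue: "An Odds ratio for an UTI will be attributed to each confounder based on a critical literature appraisal". No odds ratios are given. Nothing says how they would enter the model or how their uncertainty would be carried.

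Section 3.1 describes the same analysis differently. It announces multivariable logistic regression: "First a crude model will be used followed by confounder adjusted models". There the literature decides which variables are included: the confounders are season and "risk factors for UTI and selected based on theory or literature". No effect sizes are imported.

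For the secondary outcome, section 6.2 says of the Cox model: "The hazard ratio will be adjusted with the previous described confounders".

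Section 3.5 lists what is extracted per patient, for example "History of UTI ICPC code U70, U71". It gives codes for six of the seven risk factors in 6.2. Pregnancy is not listed.

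**The concern.** Selecting a confounder from the literature is standard. Taking its coefficient from the literature is a different step, and it calls for a reason when the variable is recorded in the study's own data. A published odds ratio reflects its own population, UTI definition and adjustment set, and odds ratios are not collapsible across adjustment sets. Here the data are also selected: section 5.1 requires an acute UTI for inclusion, so a published contrast between people with and without UTI may not be the relevant one.

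At stake is the primary estimate. If a borrowed value is too small, part of the confounding stays in the antibiotic odds ratio. If it is too large, the estimate is pushed past the truth. In both cases the reported interval treats the borrowed value as known. Section 6.1 also runs the model in men, in women under 50 and in women of 50 and over. One value per confounder could be wrong by different amounts in each group and so produce apparent differences between them.

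**Working it through.** **No figure to reproduce.** The protocol states no event rate, prevalence, sample size or literature odds ratio. The calculation below shows the mechanism only; every input is assumed.

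**Inputs (assumed).** One binary confounder C, prevalence 30%. UTI risk 3% when C = 0. Antibiotic exposure 10% when C = 0. No antibiotic effect (true odds ratio 1). Between-person logistic model. The literature odds ratio enters as a fixed coefficient.

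**One case by hand:** local C–UTI odds ratio 4, literature value 2, C–exposure odds ratio 2.

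1. Exposure when C = 1: odds 2 × 0.10/0.90 = 0.2222, probability 0.1818.
2. P(exposed) = 0.7 × 0.10 + 0.3 × 0.1818 = 0.1245. Hence P(C = 1 | exposed) = 0.05455/0.1245 = 0.438 and P(C = 1 | unexposed) = 0.2455/0.8755 = 0.280.
3. Risk when C = 1: odds 4 × 0.03/0.97 = 0.1237, risk 0.1101.
4. Risk if exposed: 0.562 × 0.03 + 0.438 × 0.1101 = 0.0651. If unexposed: 0.720 × 0.03 + 0.280 × 0.1101 = 0.0525.
5. Unadjusted odds ratio: (0.06508/0.93492)/(0.05246/0.94754) = 1.26.
6. With C fixed at 2, the score equations make fitted risk equal observed risk in each exposure group. Solve (1 − q)·o/(1 + o) + q·2o/(1 + 2o) = risk for the baseline odds o, where q is P(C = 1) in that group. Exposed: o = 0.04879. Unexposed: o = 0.04351. Antibiotic odds ratio = 0.04879/0.04351 = 1.12, where the truth is 1.

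**The same calculation over a range:**

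| Local OR | OR imposed | C–exposure OR 1.5 | 2 | 3 |
|---|---|---|---|---|
| 4 | none (unadjusted) | 1.14 | 1.26 | 1.43 |
| 4 | 1.5 | 1.10 | 1.18 | 1.29 |
| 4 | 2 | 1.07 | 1.12 | 1.19 |
| 4 | 3 | 1.03 | 1.05 | 1.07 |
| 4 | 4 | 1.00 | 1.00 | 1.00 |
| 2 | 2.5 | 0.98 | 0.96 | 0.94 |
| 2 | 4 | 0.93 | 0.89 | 0.84 |

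On the log scale, a literature value of 2 against a local 4 leaves about half of the confounding: ln 1.121/ln 1.257 = 0.114/0.229 = 0.50.

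**Intervals.** A separate simulation used 2,000 runs per setting, prevalence 30%, exposure 20%, baseline risk 5%, local odds ratio 4 and a true antibiotic odds ratio of 1.5 (all assumed). The literature value was unbiased but uncertain, with a standard error of 0.3 on the log scale. Coverage of the nominal 95% interval, for C–exposure odds ratios of 2 and 3:

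- N = 5,000: 93% and 89% with the fixed value.
- N = 50,000: 78% and 60% with the fixed value.
- Coefficient estimated in the data: 94% to 96% in all four settings.

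In a companion run at N = 50,000 with no antibiotic effect and a C–exposure odds ratio of 2, the model standard error was 0.0362 with the value fixed at 4 and 0.0366 with it estimated. The fixed-value interval therefore carries none of the external uncertainty, and a larger sample makes the shortfall worse.

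**The case against.** The strongest objection is that fixed coefficients are an inference. Section 6.2 names no offset, constraint, weight or score, and section 3.1 describes ordinary estimation. The sentence might only mean a table of published effect sizes that supports the choice of confounders. This stands in part: the mechanism is unstated. But selection is already covered in 3.1, and the sentence sits inside the primary model specification. Its plain meaning is that effect sizes come from outside, so it needs correcting on either reading.

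The second objection concerns the design. Section 3.1 calls the study a self-controlled case series, and in a truly conditional within-person analysis time-fixed risk factors cancel whatever value they are given. This also stands as a limit on the illustration. Section 6.2, however, does not describe its logistic model as conditional, and it lists these factors as confounders.

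The third is that the larger figures need literature values wrong by a factor of 2 or more. Smaller errors do less harm, as the rows 4 against 3 and 2 against 2.5 show. At 5% prevalence, local 4 against literature 2 gives only 1.03 to 1.11. Errors across seven factors may also partly offset, so their number does not imply that bias accumulates.

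Two further inferences are tempting but unsupported. One is that odds ratios would be imposed in the Cox model: the text carries over the confounders and does not say that their values come along. The other is that every covariate is observed: pregnancy is absent from the 3.5 list, and so are the immunocompromising conditions that 3.1 names.

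**Conclusion.** Sections 3.1 and 6.2 give different accounts of the primary adjustment, and the account in 6.2, read plainly, is the poorer one. If it is followed, confounding is removed incompletely or over-corrected wherever a borrowed value differs from the local conditional effect, and the interval ignores the uncertainty of that value. There is no bias if the two agree, but the protocol gives no reason to expect agreement for all of the listed factors.

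A reader might infer that the study's antibiotic odds ratio will be off by the amounts tabulated. The document does not support that. The figures rest on one assumed confounder in a between-person model, and both the direction and the size depend on values that the protocol does not give. What is established is the conflict between the sections and the consequence of following 6.2. Because it touches the primary estimate, it should be settled before the analysis.

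**What to change.** Delete the sentence in section 6.2 and replace it with text in line with 3.1, for example:

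*The literature is used only to choose confounders. The coefficients of all confounders in the model are estimated from the ELAN data together with antibiotic exposure, in both the logistic and the Cox model. Published odds ratios may be shown beside the estimates as a plausibility check only.*

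Also reconcile the confounder list with the extract. Pregnancy is a named confounder but is not listed in 3.5, so add it to the extract or remove it from the confounder list. Section 5.2 excludes UTIs during pregnancy as events, so that information is needed for the exclusion in any case. The immunocompromising conditions appear in 3.1 but in neither 6.2 nor 3.5, and need the same decision.

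The cost is a short text change, possibly an addition to the data request, and less work on appraising published effect sizes. There is one small downside: with the planned combinations of subgroups across ten antibiotic groups, and no sample size stated, estimated coefficients may be unstable in sparse cells.
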